### Self-reported physical activity

Self-reported physical activity is measured with questions that evaluate participants’ physical activity level during the last seven days at moderate intensity and vigorous levels. Questions include all the activity for which the physical effort is moderate or harder, including transportation to work and leisure time physical activity [17]. During the accelerometer measurements participants will also keep a diary, which includes the type and duration of physical activity.

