#### The Acceptance and Commitment-based Group (ACT + FB)

The Acceptance and Commitment-based group (ACT + FB) will be subject to the same procedures as the feedback group. In addition, they will participate in the ACT-based program and be given a pedometer for self-monitoring of their daily physical activity during the intervention program. The intervention program consists of six group sessions during the 9-week period of time, with each session lasting about 90 minutes (see Table 1). The sessions will be led by three to five group leaders, including the researcher. The group size is 8–10 participants per one group. All the group leaders will be trained in the ACT approach and supervised by the responsible researcher (AK). Participants will also get their own workbook, which will contain short descriptions of the sessions, and all individual reflections and notes.

**Table 1 T1:** Content of the six group sessions in the Acceptance and Commitment-based group

**Topics of the group sessions**	**Key points and aims of the sessions**
1. Health behaviour	What are the factors affecting my health behaviour/well-being? What is the direction I want to move in? What are the steps I have taken in order to try to change my well-being?
2. Values and important things in life	What are the most important values for me?
	Am I living or behaving according to my values?
3. Value-based actions and barriers	What are my specific goals and actions that support my valued behaviour?
	What kind of subjective barriers or explanations have I related to physical activity?
4. Living in the present moment and self-regulation skills	How do I contact the present moment?
	How do I use mindfulness skills in order to be more aware of my own behaviour in everyday life?
5. Self-processes and physical activity	How do I see myself and how does it affect my behaviour?
	Can I be more aware of the way I am thinking about myself and learn nonreactive ways to respond to these thoughts?
6. Flexible actions	How am I doing? What are the actions which help me to achieve my desired outcomes? Do I need to change my goals? Am I living according to my values?
	Can I be more flexible in my behaviour and physically active lifestyle?

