The program aims to enhance physically active lifestyles and well-being through important life values and build committed action based on the chosen important values. The program will start with an analysis of health behaviour and reflections about values and important things in life. After value clarification, participants will make concrete action plans and define their own goals. The emphasis will be placed on small and feasible everyday actions, rather than demanding exercise goals. In order to achieve the set goals, participants are taught mindfulness skills and new ways to deal with the barriers. The purpose of learning mindfulness skills is to be more aware of one’s own thoughts, emotions and automatic behaviour patterns. By noticing these automatic thinking styles or routines, participants will have a better ability to consciously change their own behaviour in the everyday life context.

Every session includes mindfulness exercises, pair and group discussions and homework related to the topic of the session. The intention of homework is to encourage participants to also work with the topics between the sessions and transfer learnt skills into their own living context. The group leader’s role is to introduce the topics, teach new skills, lead the ongoing discussion and provide a context in which participants are willing to share their own experiences, thoughts and feelings. The program does not include psycho-educational elements, counseling on health, information about the health benefits of physical activity, or concrete physical exercise.

Table 1 Content of the six group sessions in the Acceptance and Commitment Therapy (ACT) intervention group.

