### Outcome measures

Measurements will take place at baseline and 3, 6, 9, and 15 months after the baseline (Figure 1). The baseline demographic characteristics of participants will also be recorded. The primary outcome measures will be based on physical activity.

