### Sample size

Power calculations were performed in order to determine the sufficient sample size to detect the significant intervention effect at a significance level of α = 0.05. Analysis was conducted for one of the primary outcome measures, objectively measured time spent in health-enhancing physical activity (HEPA time, min/day). A sample size of 100 (50 per group) would be sufficient to detect a medium-sized effect at the power level of 85%. In this case, a difference in a change in the HEPA time between the ACT + FB and FB groups equal to 5 minutes per day would be detected at appropriate levels of statistical power. Power calculations were based on Monte Carlo simulation studies and were performed by using the Mplus statistical package [32].

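### Self-reported 7-day activity appears to be a primary outcome beside the accelerometer, although participants know their arm and only ACT + FB is treated in ways that could change how activity is reported

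*Protocol article*

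**What the plan says.** Under Outcome measures, the Protocol article states: "The primary outcome measures will be based on physical activity". The heading Primary outcome measures then opens with the accelerometer. Next comes the section Self-reported physical activity, which opens with this sentence: "Self-reported physical activity is measured with questions that evaluate participants’ physical activity level during the last seven days at moderate intensity and vigorous levels". That section adds: "Questions include all the activity for which the physical effort is moderate or harder, including transportation to work and leisure time physical activity". It also describes an activity diary kept during the accelerometer weeks. Secondary outcome measures begin only after this.

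On the ACT + FB arm, the article says that its members will "be given a pedometer for self-monitoring of their daily physical activity during the intervention program". Of the group programme it says "The sessions will be led by three to five group leaders, including the researcher", and that "participants will make concrete action plans and define their own goals". The programme also teaches mindfulness so that participants become more conscious of their own habits and behaviour. The FB arm receives its activity feedback by post, without personal contact. Both arms are offered a body composition visit with a short personal interpretation.

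The Statistical analysis section tests the intervention effect on primary and secondary outcomes at 0.05, with control for baseline differences. It does not rank self-report below the accelerometer.

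**The concern.** Participants cannot be unaware of whether they attend six group sessions, and for a recall questionnaire the participant is the assessor. The treatment works directly on self-observation and commitment to action, in a setting where staff, including the researcher, lead the groups. It could change what a participant notices, remembers or is willing to report, whether or not activity itself changes. That would be measurement error that differs between arms because of the treatment, and randomisation does not protect against it.

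At stake is the efficacy claim. If recall has primary status, a self-report difference with no matching accelerometer difference could be presented as a positive primary result. A measure that does not depend on recall is already planned for both arms at every wave, so the claim need not carry this risk.

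**Working it through.** **1. Is self-report primary?** The relevant parts of the Protocol article, in order:

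- Outcome measures: the primaries are described by domain (physical activity), not by a single variable.
- Primary outcome measures: the accelerometer comes first, nested under this heading.
- Self-reported physical activity: follows directly, but in the text at hand its heading is at the same level as the primary and secondary headings.
- Secondary outcome measures: exercise beliefs and intentions, psychological and depressive symptoms, mindfulness, psychological flexibility. No activity measure appears here.
- Sample size: HEPA time is described as one among several primary measures.

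Self-report measures physical activity, precedes the secondary list and is absent from it. Primary is the natural reading. The heading level leaves some doubt and may come from text extraction.

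**2. What differs between arms?**

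| Element | ACT + FB | FB |
|---|---|---|
| Six staff-led sessions of about 90 minutes | yes | no |
| Training in noticing own behaviour | yes | no |
| Action plans and own goals | yes | no |
| Pedometer during the 9-week programme | yes | no |
| Activity diary in accelerometer weeks | yes | yes |
| Written activity feedback after each wave | yes | yes |
| Body composition visit offered | yes | yes |

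The contrast is clear for sessions, awareness training and goal setting. For self-monitoring it is one of degree.

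**3. Does baseline adjustment help?** Let D be the true difference in activity, and let b be the mean reporting shift caused by treatment in ACT + FB minus that in FB. The expected between-arm difference in self-report is D + b. Reports made before the programme contain no part of b, so adjusting for them leaves b in place. A larger sample narrows the standard error but does not shrink b.

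**4. The plan's own figure.** Sample size gives 85% power with 50 per group for a medium effect (d = 0.5 on the article's scale). With a normal approximation, the standard error in SD units is sqrt(2/50) = 0.20 and power is Φ(0.5/0.20 − 1.96) = Φ(0.54) = 70.5%. With baseline adjustment at an assumed correlation of 0.55, the standard error is 0.20 × sqrt(1 − 0.55²) = 0.167 and power is Φ(0.5/0.167 − 1.96) = 84.9%. The article's figure comes from a simulation whose SD and correlation are not given, so it is neither confirmed nor shown wrong. The point here does not depend on it.

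**5. Illustration of sensitivity.** Assume D = 0, 50 per group, two-sided 0.05, and b > 0 in SD units of the self-report measure. The chance of a significant result favouring ACT + FB is Φ(b/SE − 1.96):

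| Assumed b (SD) | SE 0.20 (no adjustment) | SE 0.167 (correlation 0.55) |
|---|---|---|
| 0 | 2.5% | 2.5% |
| 0.1 | 7.2% | 8.7% |
| 0.2 | 16.9% | 22.3% |
| 0.3 | 32.3% | 43.5% |

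Both b and the correlation are assumptions. If b were negative, the same figures would apply to a result favouring FB, and a true benefit could be masked.

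**The case against.** The strongest reply is that the arms are closer than they look. Both keep the diary, both receive activity feedback after each wave, and both are offered a visit with personal feedback. Participants define their own goals, with emphasis on small everyday actions. The pedometer belongs to the 9-week programme, whereas follow-up runs to 15 months. This stands: it is not correct to infer that only one arm monitors itself, or that FB has no personal contact. The sessions, awareness training and goal setting still differ.

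Second, the primary status of self-report is inferred, and a ranking of primaries or a rule for discordant results may be in an analysis plan that is not shown. Also, the accelerometer is listed first and HEPA time sizes the trial, so discordance would be visible. The uncertainty is fair. However, the point concerns the status that the article itself appears to give to recall, not a missing rule.

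Third, a reader might infer that ACT + FB will over-report and might set a guessed number of minutes against the 5 min/day in the Sample size section. The documents support neither step. Awareness training and step counts could instead make recall more accurate and lower the reports. The 5 min/day is an accelerometer HEPA target, and no SD or target is given for self-report, so that ratio would have no meaning.

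Fourth, a reader might treat the gap between self-report and accelerometer, by arm, as a test of reporting bias. It is not one: a real rise in cycling or swimming, which a hip device captures poorly, would widen the gap in the same way.

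**Conclusion.** The point holds as a cheap improvement to the outcome wording, not as an error or contradiction. On the natural reading, an outcome assessed by participants who know their arm has the same status as the accelerometer, and the treatment given to one arm could alter reporting. Baseline adjustment would not remove such a shift. Its direction and size cannot be estimated from the documents. The illustration shows only that a modest shift would matter: 0.2 to 0.3 SD in favour of ACT + FB, with no true effect and 50 per group, gives a 17-44% chance of a significant result in that direction instead of 2.5%. The verdict rests on self-report being primary, which the order of the sections and the description of the primaries support, and on participants knowing their arm, which follows from the interventions although the article does not discuss blinding. The accelerometer outcomes do not depend on recall and are not put in doubt by this point.

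**What to change.** In Outcome measures, Primary outcome measures and Self-reported physical activity:

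- State that the efficacy conclusion on physical activity rests on the accelerometer, specifically HEPA time, which already sizes the trial.
- List the self-report questions and the diary as secondary, supportive outcomes.
- State that no activity effect will be claimed from self-report alone.

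If self-report and accelerometer are compared by arm, label the comparison descriptive.

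The cost is a change of wording, with no new data collection. The downside is small: activity that a hip-worn device captures poorly, such as cycling or swimming, becomes supportive evidence only.

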### Secondary outcome measures

#### Beliefs and intentions for exercise

Intentions and beliefs for physical activity are measured with the questionnaires, which measure adoption self-efficacy concerning physical activity with five items [22], barriers regarding exercise with five items [22], action planning for exercise with four items and coping planning for exercise with four items [23]. Response alternatives range from 1 (very certain I cannot) to 4 (very certain I can).

#### Psychological and depressive symptoms

Psychological symptoms are measured with the General Health Questionnaire (GHQ-12), which has been widely used to evaluate psychological distress in population-based studies. GHQ-12 is the shortened version of the GHQ-60 and GHQ-36, which has produced results comparable to the longer versions of the GHQ [24]. It contains 12 items describing psychological distress, responding to “how a subject feels about their present state over the past few weeks”. The scale has a four-point response scale, which was scored using a bimodal scale (0, 0, 1, 1) on the basis of the presence of symptoms: “not at all” (0), “same as usual” (0), “rather more than usual” (1), and “much more than usual” (1). The total score, obtained by summing the scores of the individual items, is a measure for severity of illness.

Psychological symptoms are also measured with the Symptom Checklist-90, SCL-90 [25,26]. Participants are asked to score the questionnaire’s 90 items using a five-point Likert scale, indicating the rate of occurrence of the symptoms during the time reference. The instrument’s global index of distress is the Global Severity Index (GSI), which is the mean value of all of the items.

Depressive symptoms are measured with the Beck Depression Inventory, BDI-II [27,28]. The BDI-II is a 21-item scale measuring depression symptoms, including components from cognitive, behavioural, affective, and somatic aspects. Based on the scores, depressive symptoms can be categorised into no/minimal depression (0–13 points), mild depression (14–19 points), moderate depression (20–28 points), and severe depression (29–63 points) levels.

#### Mindfulness skills

The ability to be in the present moment is measured using the Kentucky Inventory of Mindfulness Skills, KIMS. The KIMS is a 39-item self-report inventory used to assess mindfulness skills. The questionnaire contained four different specific subscales or skills: 1) observing, 2) describing, 3) acting with awareness, and 4) accepting without judgment [29]. *The observing* subscale involves observing, noticing, or attending to various stimuli, including internal (cognitions, bodily sensations) and external phenomena (sounds, smells). *The describing* subscale measures participant ability to describe, label, or notice observed phenomena by applying words in a non-judgmental way. The *acting with awareness* subscale measures ability to be attentive and engage fully in one’s current activity. The subscale of *accepting without judgment* measures how reality is allowed without judging, avoiding, changing, or escaping from it. Participants rated each item on a 5-point Likert type scale ranging from 1 (never or very rarely true) to 5 (almost always or always true). Items reflected either direct descriptions of the mindfulness skills or the absence of that skill, and were reverse scored [29].

#### Psychological flexibility

Psychological flexibility is assessed using the Acceptance and Action Questionnaire, AAQ-2 [6], which is a 10-item Likert-type questionnaire that assesses individuals’ ability to take a non-elaborative, non-judgmental approach to their internal events, so that they can focus on the present moment and act in a way that is congruent with their values and goals, rather than with their internal events (e.g., fears, urges, prejudices). The questions of the AAQ-2 are based on the following statements: 1) It’s okay if I remember something unpleasant, 2) My painful experiences and memories make it difficult for me to live a life that I would value, 3) I’m afraid of my feelings, 4) I worry about not being able to control my worries and feelings, 5) My painful memories prevent me from having a fulfilling life, 6) I am in control of my life, 7) Emotions cause problems in my life, 8) It seems that most people are handling their lives better than I am, 9) Worries get in the way of my success, and 10) My thoughts and feelings do not get in the way of how I want to live my life. The AAQ has been reported to have good reliability and validity [30,31].

### Statistical analysis

Data will be analyzed using the Mplus statistical package 7.1 [32]. The intervention effect on primary and secondary outcome measures will be estimated and tested for significance. Analyses will be controlled for possible baseline differences between the ACT + FB and FB groups. Cohen’s *d* will be used to estimate the effect size of the intervention effect. An effect size of 0.2 is considered small, 0.5 is medium, and 0.8 is large [33]. Furthermore, differences in the stability of the outcome measures between the ACT + FB and FB groups will be examined using multiple-group modeling techniques. Full information maximum likelihood (FIML) estimation under the assumption of data missing at random (MAR) will be used in analyzing incomplete data. As the normality assumption is violated, maximum likelihood with robust standard errors (MLR) will be used. The significance level of the study will be set at 0.05.

### Sample size

Power calculations were performed in order to determine the sufficient sample size to detect the significant intervention effect at a significance level of α = 0.05. Analysis was conducted for one of the primary outcome measures, objectively measured time spent in health-enhancing physical activity (HEPA time, min/day). A sample size of 100 (50 per group) would be sufficient to detect a medium-sized effect at the power level of 85%. In this case, a difference in a change in the HEPA time between the ACT + FB and FB groups equal to 5 minutes per day would be detected at appropriate levels of statistical power. Power calculations were based on Monte Carlo simulation studies and were performed by using the Mplus statistical package [32].

## Discussion

This article demonstrates the research protocol for a randomized controlled study focused on motivating physically more active lifestyles among physically inactive adults based on individuals’ own values. The study will assess the impact of intervention on physical activity levels and psychological well-being, and discuss the challenges and methodological problems in studying physically inactive participants.

Many authors have expressed the need for new theories and effective interventions to enhance physical activity [4]. To our knowledge, this is the first study focusing on motivating physically more active lifestyles by using value- and mindfulness-based approaches in combination with monitoring physical activity. This approach does not include traditional counseling or psycho-educational elements. Instead, the focus is on mindful behavioural change, and well-being and individual motivation based on one’s own values in life. Working with values and value clarification will provide ongoing direction and long term outcome goals in life. Instead, the actions are defined more as process goals, which can be set in the short term. Importance is also placed on the functions of the actions and the practices that work in order to achieve a meaningful life.

The study will provide novel information about new methods for motivating physically more active lifestyles and related challenges in conducting the study (e.g., recruiting physically inactive adults). In this study, the study population is limited to physically inactive adults. This is a very important starting point if the goal is to evaluate the workability of methods, which aims to motivate physically active lifestyles. The methods that work for physically more active adults may not be the best way to motivate least active ones. In addition, in practice it may be a challenge to find these physically inactive participants and get them involved. Methodologically it may also be demanding to keep the feedback group in the study, because they will receive the minor intervention. The study will provide more information of the psychological well-being of the physically inactive adults, which may be have an important role behind the physically active behaviour change. In addition, the qualitative and quantitative analysis of participants’ experiences will be of importance.

In conclusion, the study will explore the feasibility and efficacy of feedback and ACT based approaches in motivating physically more active lifestyles among physically inactive adults. The study will also examine the effectiveness on psychological well-being. The results will be discussed in the light of the ACT model and based on cognitive behavioural learning theories in order to bring new and alternative approaches to the field.

## Abbreviations

ACT: Acceptance and commitment therapy; FB: Feedback; CPM: Counts per minute; LPA time: Light intensity physical activity; LIFEPA: Lifestyle physical activity; MVPA: Moderate-to-vigorous intensity physical activity; HEPA: Health-enhancing physical activity; GHQ-12: General health questionnaire; SCL-90: Symptom Checklist-90; BDI-II: Beck depression inventory; KIMS: Kentucky inventory of mindfulness skills; AAQ-2: Acceptance and action questionnaire.
